### Missing data

The extent and patterns of missing data will be assessed for all key variables. Variables with more than 5% missing observations will be reported explicitly. For EORTC questionnaires (QLQ-C30 and QLQ-EN24), missing items will be handled according to the EORTC scoring manuals. Scale scores will be calculated when at least half of the items contributing to a scale have been completed; missing items within eligible scales will be replaced by the mean of the completed items from that scale. If fewer than half of the items are completed, the scale score will be considered missing. Complete-case analyses will be used for primary analyses. Additional sensitivity analyses may be considered if the extent of missing data is substantial and the number of observations permits.

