**Methods and analysis:**

This multicentre prospective observational cohort will enrol patients diagnosed with SEIC or equivalent non-invasive serous lesions who provide informed consent. Data will be collected using electronic case report forms (Castor Electronic Data Capture). Baseline clinical, pathological, molecular and treatment data will be collected, including imaging, histopathology, immunohistochemistry and molecular classification when available. Patient-reported outcomes will be assessed using the European Organisation for Research and Treatment of Cancer Quality of Life Questionnaire Core 30 (EORTC QLQ-C30), European Organisation for Research and Treatment of Cancer Quality of Life Questionnaire Endometrial Cancer Module (EORTC QLQ-EN24) and EuroQol 5-Dimension 5-Level questionnaire (EQ-5D-5L) questionnaires at baseline, 6 months, 2 years and 5 years after diagnosis. The primary outcome is progression-free survival, secondary outcomes include overall survival, health-related quality of life and adverse events. Analyses will be primarily descriptive. Survival outcomes will be estimated using Kaplan-Meier methods, with Cox proportional hazards modelling used to explore predictors of outcome where feasible.

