#### Case identification and recruitment

Patients will be enrolled by the principal investigator, the coordinating investigator or the research nurse of the Erasmus Medical Center, after signed informed consent was obtained at one of the participating centres. Patients will be informed by their primary clinician (gynaecologist) and provided with a patient information brochure. If the patient is interested in participating, a hardcopy informed consent form is provided or a link to ValidSign^21^ via email will be sent, where a special PDF version of the informed consent form is available. The participant can sign this with an ‘advanced electronic signature’ with SMS verification. The digital consent form will then be downloaded to a secure drive on the Erasmus MC network for archiving. From all participants who provided written informed consent in a participating centre, the signed form will be scanned and stored digitally in the participating centre. All clinical data are prospectively collected through electronic case report forms (e-CRF) by the treating gynaecologist of the participating centre. The coordinating investigator will re-evaluate the provided data and ensure that collecting data is complete. All participants will receive an online questionnaire using a survey package in Castor Electronic Data Capture (EDC) at the time of diagnosis and during follow-up after 6 months, 2 years and 5 years of diagnosis, respectively. The survey package includes three online questionnaires: EQ-5D-5L QOL, QLQ-EN24 and QOL-C30. The estimated time needed to complete the three questionnaires is 15 min. Regarding therapy of SEIC, all treatment options are allowed (surgery, systemic therapy, radiotherapy). There will be no specific, patient-tailored recommendations regarding the given therapy. All interventions are part of regular medical treatment and are registered. The methods are all part of standard clinical care, apart from the collection of data through the questionnaires. Since this is an observational study, no interventions are performed.

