### Data collection and data management

#### Data collection

All eligible patients who provide informed consent will be included in a secure online database using Castor EDC. Clinical data will be collected through e-CRFs completed by the treating gynaecologist at the participating centre. The coordinating investigator will review all entered data to ensure completeness and consistency. Participants will complete validated online questionnaires via Castor EDC at baseline (prior to treatment, if applicable), and at 6 months, 2 years and 5 years after diagnosis.

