### Statistical analysis

Baseline characteristics, treatment details and outcome measures will be analysed using descriptive statistics. Continuous variables will be summarised using means and SD or medians and IQRs, as appropriate. Categorical variables will be presented as frequencies and percentages. Longitudinal QoL scores will be summarised descriptively over time. Comparisons between groups, if applicable, will be performed using the χ² test or Fisher’s exact test for categorical variables and the unpaired T-test or Mann-Whitney U test for continuous variables, depending on data distribution. If subgroup analyses are feasible, patients will be stratified according to the extent of surgical treatment (eg, complete surgical staging vs hysterectomy with bilateral salpingo-oophorectomy only). PFS and OS will be estimated using the Kaplan-Meier method, and differences between groups will be assessed using the log-rank test. Survival analyses will use the date of histopathological diagnosis as the index date. Univariate Cox proportional hazard regression analyses will be performed to explore potential predictors of survival outcomes. Multivariable Cox regression analysis will be conducted only if the number of events allows reliable modelling. Results will be reported as HRs with 95% CIs. All statistical analyses will be performed using the SPSS, V.25.0. A two-sided p<0.05 will be considered statistically significant.

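### Complete-case analysis is fixed as primary and earlier quality-of-life scores go unused, so later quality-of-life means are open to bias from health-related non-response

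*Protocol article*

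**What the plan says.** The Missing data section states: "Complete-case analyses will be used for primary analyses". The alternative is optional and names no method or trigger: "Additional sensitivity analyses may be considered if the extent of missing data is substantial and the number of observations permits". The same section provides for a check of missing-data patterns, for disclosure ("Variables with more than 5% missing observations will be reported explicitly") and for item-level gaps in the EORTC scales ("missing items within eligible scales will be replaced by the mean of the completed items from that scale", where at least half the items were answered). It says nothing specific about a questionnaire that is not returned at all.

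Under Statistical analysis, "Longitudinal QoL scores will be summarised descriptively over time". Group comparisons of continuous variables use an unpaired t-test or Mann-Whitney test. There are four questionnaire waves: baseline, 6 months, 2 years and 5 years.

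Baseline timing is described in two ways. Case identification and recruitment sends the questionnaires "at the time of diagnosis and during follow-up after 6 months" and at the later waves. Data collection places the first one "at baseline (prior to treatment, if applicable".

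**The concern.** QoL is a secondary outcome, but it is part of the hypothesis at the end of the Introduction: less extensive surgery may give similar oncological results while preserving QoL. The 2- and 5-year scores are therefore the ones readers will look to.

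A mean over responders is right for all living patients only if response is unrelated to the score. If patients in poorer health respond less often, the later means are too favourable. If that pattern differs between surgical groups, the difference between groups is distorted as well. A patient's own earlier scores carry information about the missing one, but a wave-by-wave summary or an unpaired test ignores them. The fallback also depends on having enough observations, so it is least available when missingness is worst.

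Baseline timing is a separate measurement problem. A score taken after surgery is not a pre-treatment reference, and no missing-data method makes it one.

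**Working it through.** **Inputs from the article.** The Sample size calculation section expects about 100 eligible Dutch patients and about 75% consent: 100 × 0.75 = 75. It gives no power, event count or expected missing rate, so there is no such figure to reproduce. It also cites 77 registered patients between 2015 and 2025. Taken as 10 years, that is 7.7 per year, or 38.5 in 5 years, of whom 75% is about 29.

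**Assumptions.** Missing rate m per wave of 10, 20 or 30%, independent between waves; score SD of 20 points.

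**Patients kept.** Wave by wave: N(1 − m). All four waves required: N(1 − m)^4. The 95% CI half-width for a mean is 1.96 × 20/√n, computed before n is rounded.

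| N = 75 | Kept per wave | Half-width | Kept if all four required | Half-width |
|---|---|---|---|---|
| m = 10% | 75 × 0.9 = 67.5 (68) | 4.8 | 75 × 0.656 = 49 | 5.6 |
| m = 20% | 75 × 0.8 = 60 | 5.1 | 75 × 0.410 = 31 | 7.1 |
| m = 30% | 75 × 0.7 = 52.5 (53) | 5.4 | 75 × 0.240 = 18 | 9.2 |

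With nothing missing the half-width is 1.96 × 20/√75 = 4.5. With N = 29 and m = 20%, 23 remain per wave and 12 if all four waves are required.

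**Bias of the 5-year mean.** This was simulated with 1,000,000 draws, SD 20, an assumed correlation of 0.6 between an earlier score and the 5-year score, and logistic non-response. The adjusted estimate regresses the 5-year score on a fully observed earlier score, a simple stand-in for a longitudinal model. Higher scores mean better QoL. At 30% missing and an odds ratio of 2 for non-response per SD worse:

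- Non-response depends on the earlier score: responder mean +2.3 points; using the earlier score, 0.0.
- Non-response depends on the unseen 5-year score: +3.8 points; using the earlier score, +2.5.

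Across 20 to 40% missing and odds ratios of 1.5 to 3, responder bias runs from +1.0 to +4.3 points in the first case and from +1.6 to +7.1 in the second. It is 0 when non-response is unrelated to the score (odds ratio 1).

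**Survival models.** Kaplan-Meier estimation keeps patients without an event as censored, and Withdrawal and data retention generally allows data up to withdrawal to be used. Complete-case loss arises only where a covariate is missing, for example "immunohistochemistry and molecular classification when available". At an assumed 10% missing, a univariate Cox model keeps 75 × 0.9 = 67.5, about 68. A five-covariate model with independent gaps would keep 75 × 0.9^5 = 44, but multivariable modelling is conditional on the event count and no number of covariates is given.

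**Baseline.** The Sample size calculation section describes diagnosis following polyp resection, so a questionnaire sent at diagnosis can come after a procedure. Collected variables includes the date of surgery.

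**The case against.** The case against is strong in several places.

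- **Primary outcome.** A reader might infer that complete-case analysis shrinks the progression-free survival analysis. It does not: censoring handles incomplete follow-up.
- **Size of the loss.** A reader might take 31 or 18 of 75 as the expected analysis set. No stated analysis requires all four waves, and the natural reading of a descriptive summary is wave by wave, which keeps 60 or 53. Large losses in a many-covariate Cox model are likewise not planned. With no recurrences among 23 patients in the group's retrospective series, such a model may never be fitted.
- **Missingness as fact.** Substantial, health-related missingness is plausible over 5 years, but no rate is given. Absent molecular results reflect test availability, and Pathology data and biological material allows missing tests to be added. Non-response that depends only on surgical group would leave within-group means unbiased.
- **Survivors.** Restriction to the living is not caused by complete-case analysis. Patients who have died have no later score under any method, and a while-alive analysis shares the restriction.
- **Baseline.** A reader might infer that pre- and post-operative baselines will be pooled, or that this makes surgery look harmless. Pooling is not stated, no change-from-baseline analysis is announced, and the wording shows awareness that some baselines cannot precede treatment.
- **Scope.** The registry is mainly descriptive, QoL is secondary, and details may sit in a fuller plan that is not shown.

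All of this narrows the point. It does not remove it: the article itself names complete-case as the primary method, and its stated QoL methods make no use of earlier scores.

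**Conclusion.** The point holds for longitudinal QoL and, to a lesser degree, for any covariate model. It does not hold for the Kaplan-Meier estimates. The bias is conditional: under the assumed correlation, SD and missing rates it is about 1 to 4 points when non-response follows earlier scores, up to about 7 when it follows the unseen score, and nil when it is unrelated to health. The loss of precision is modest if a complete case is defined per wave (half-width 5.1 against 4.5 points at 20% missing) and clear if all four waves are required (7.1). The article does not settle which applies. Mixed baseline timing is permitted by the text and has no stated handling; it is a separate and smaller matter. The change is worth making because it costs little and QoL is part of the hypothesis.

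**What to change.** 1. Make a linear mixed model for repeated measures the primary longitudinal QoL analysis, using all scores available while alive, with time, surgical group and their interaction if group sizes allow.
2. Keep complete-case analysis as a sensitivity analysis and say what a complete case is in each analysis. Because the mixed model assumes data missing at random, add a sensitivity analysis for non-response that depends on the unseen score.
3. Report the numbers alive and the numbers responding at each wave, so that death and non-response can be told apart.
4. Flag each baseline questionnaire as before or after surgery from the recorded dates, summarise the two kinds separately, and use only pre-surgery scores as baseline in any change analysis.
5. Consider multiple imputation of covariates only if a multivariable Cox model proves feasible; with few events it may be unstable.

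The cost is changed wording, one derived variable and slightly more analysis work, with mixed models available in SPSS. The drawbacks are reliance on the missing-at-random assumption and fewer patients in any change-from-baseline summary.

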### Study status

Participant recruitment started in May 2026 and is expected to be completed in April 2031. On 1 February 2026, 10 participating centres are involved. We are open to more collaborations, nationally and internationally.

## Ethics and dissemination

Central study approval was obtained at the Erasmus MC (MEC-2025-0368). Results of this study will be published in peer-reviewed journals and will be shared in reports of relevant conferences and congresses. All principal investigators of participating centres are joined in the SEIC Study Group, to share expertise on this topic. Researchers contributing to study conceptualisation, design, data collection, analysis and writing or reviewing of the manuscript are listed as authors.

### Patient and public involvement

Patients or the public are not directly involved in the design of the study or its implementation.
